**RESULTS ANALYSIS**

Initial descriptive analyses will be performed considering all variables measured in the study, both quantitative (mean and standard deviation) and qualitative (frequencies and percentages). If the data follow a normal distribution, they will be subjected to two-way ANOVA, and the data will be presented as means ± standard deviation (SD). Otherwise, they will be presented as medians and interquartile ranges and compared using the Kruskal-Wallis test. Categorical variables will be evaluated using the chi-square test, Fisher's exact test, or the likelihood ratio test. For all tests, a 5% significance level or the corresponding p-value will be adopted. All analyses will be conducted using the SAS for Windows statistical program, version 9.1.

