**2.2. Specific Objectives**

**•** To evaluate complete remission (100% remission) of the lesions in relation to the initial number of facial lesions at 3 months (primary objective);

• To evaluate complete remission (100% remission) of the lesions in relation to the initial number of facial lesions at other time points: 30 days, 9 months, and 12 months;

• To evaluate treatment success (75% reduction in the initial number of lesions in the treatment area compared to baseline) at 30 days, 3, 6, and 12 months;

• To evaluate the recurrence rate (reappearance of lesions in previously treated areas) at 30 days, 3, 6, and 12 months;

• To prevent squamous cell carcinoma (conduct assessments to verify the occurrence of squamous cell carcinoma. Cases will be recorded and treated as necessary. Evaluations will be carried out at 30 days, 3, 6, and 12 months);

• To evaluate the incidence of adverse effects through participants’ self-completed diaries and researcher notes. Assessments will be conducted at 30 days, 3, 6, and 12 months;

• To assess postoperative pain, if it occurs, after treatments using the visual analog scale (VAS) at 0 days, 30 days, 3, 6, and 12 months;

• To evaluate the amount of analgesics consumed weekly during the first week after treatment;

• To assess improvements in skin texture, wrinkles, and pigmentation using the scale by Tina Alster et al. (2005) at 30 days, 3, 6, and 12 months;

• To assess participants' quality of life using the Actinic Keratosis Quality of Life questionnaire (AKQoL) (Vilhena et al., 2022) after 6 months of treatment;

• To assess participants' quality of life using the Face-Q questionnaire (Klassen et al., 2015) after 6 months of treatment.

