**3.7. Avaliações pré-tratamento**

After receiving the necessary explanations, participants affected by actinic keratosis who sign the Informed Consent Form (ICF) will undergo anamnesis and complete the AKQoL and Face-Q questionnaires, as well as the data collection form for the study, which will involve counting, classifying, and mapping the facial lesions. These data will be collected by the principal investigator (calibrated). Photographic records of the lesions will also be taken using a Quantificare® 3D camera and the camera of an iPhone 11 Pro Max. Following these evaluations, the treatment will be conducted according to the randomization.

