Participant Satisfaction – This will be assessed using the Actinic Keratosis Quality of Life questionnaire (AKQoL) (Esman et al., 2013) after 6 months and 1 year of treatment. The items will be scored on a standard 4-point Likert scale and summarized into a maximum score of 32 points. A higher score indicates greater impairment in quality of life. The questionnaire has been translated and validated into Portuguese (Vilhena et al., 2022).

EVALUATION OF SATISFACTION WITH FACIAL APPEARANCE (FACE-Q)

The FACE-Q scale (Satisfaction with Facial Appearance Overall) was developed by Klassen (Klassen et al., 2010) and consists of 10 items to be answered using a four-point Likert scale, which measures satisfaction with facial appearance in various scenarios. A Likert scale consists of a set of items in which the subject being evaluated is asked to indicate their level of agreement, ranging from "strongly disagree" (level 1) to "strongly agree" (level 4). The FACE-Q evaluates the perception of facial appearance in terms of characteristics such as symmetry, harmony, proportion, freshness or vitality, temporal appearance (e.g., rested facial appearance, at the end of the day, or upon waking), appearance under brighter lighting, appearance in photographs, and profile (lateral view or contour of the face). Despite being recent, the scale has already been used in several studies (Chang et al., 2016; Sinno et al., 2015; Kappos et al., 2017). Its adaptation to Brazilian Portuguese was carried out by Gama in 2018. The FACE-Q scale, validated for use in Brazil (Table 6), consists of nine items that measure two satisfaction factors (Overall facial appearance and Facial geometry). The item "With the appearance of your face at the end of the day" from the original scale was removed in the Brazilian version due to its low representativeness in the Brazilian sample, and for calculation purposes, it was also excluded from the evaluation in the present study. The sum of the scores obtained from patients' responses to the 9 items (1 = very dissatisfied, 2 = somewhat dissatisfied, 3 = somewhat satisfied, and 4 = very satisfied) can range from 9 to 36 and are converted into a score ranging from zero to 100. Higher scores indicate greater satisfaction (Table 7). The participants answered the FACE-Q questionnaire adapted to Brazilian Portuguese (Appendix C) before treatment and 30 days after its completion.

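### AKQoL and FACE-Q are scored before treatment, but the stated analysis of numeric outcomes names no adjustment for the baseline score, which costs precision on two secondary outcomes

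*Protocol*

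**What the plan says.** Section 3.7 of the Protocol states that consenting participants "will undergo anamnesis and complete the AKQoL and Face-Q questionnaires" before the randomised treatment is given. Section 3.10 describes both as numeric scores: AKQoL has a maximum of 32, and FACE-Q is converted to a scale from 0 to 100.

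The Results Analysis section covers all numeric outcomes with one rule, which the Abstract repeats. For normal data: "If the data follow a normal distribution, they will be subjected to two-way ANOVA". Otherwise: "they will be presented as medians and interquartile ranges and compared using the Kruskal-Wallis test". The section does not say what the two ANOVA factors are. It does not say whether the response is the follow-up score, a change or a set of repeated scores. It names no covariate.

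The follow-up times disagree:

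- **FACE-Q.** Section 2.2 sets the aim "To assess participants' quality of life using the Face-Q questionnaire (Klassen et al., 2015) after 6 months of treatment", and the Abstract also places it at 6 months. Section 3.10 has it answered "before treatment and 30 days after its completion".
- **AKQoL.** Section 2.2 and the Abstract give 6 months only. Section 3.10 gives "after 6 months and 1 year of treatment".

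**The concern.** A questionnaire score after treatment usually depends in part on the same person's score before it. With 36 participants per arm, the chance difference in mean baseline score between two arms has a standard error of sqrt(2/36) = 0.24 SD. In an unadjusted comparison, a share of that difference, on average the correlation times its size, carries into the follow-up result. Adjusting for the baseline score removes this noise, and the trial already collects the measurement. Quality of life is part of the Justification, and both questionnaires appear among the Specific Objectives. Wider intervals than necessary on these scores would therefore be an avoidable loss.

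**Working it through.** **The plan's own figure.** The only power statement is in section 3.1: 36 per group for complete response rates of 64% and 91%, 80% power, chi-square test. The pooled two-sided 5% formula gives

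n = [1.96 × sqrt(2 × 0.775 × 0.225) + 0.8416 × sqrt(0.64 × 0.36 + 0.91 × 0.09)]² / 0.27² = (1.157 + 0.470)² / 0.0729 = 36.3, so 37.

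Power at 36 per group is 79.6%, so the figure reproduces. It concerns lesion response, not the questionnaires.

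**Inputs for the questionnaires**

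- From the Protocol: 144 participants allocated 1:1:1:1, so 36 v 36 for a pair of arms or 72 v 72 for a factorial main effect, and a 5% significance level.
- Assumed: two-sided testing, 80% power for the unadjusted analysis, equal variance before and after treatment, and a within-arm correlation rho between baseline and follow-up of 0.3 to 0.7. The Protocol gives none of these for AKQoL or FACE-Q.

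**Formulas.** Taking the follow-up score variance as 1, the variance relevant to the group comparison is:

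- follow-up score alone: 1
- change score: 2(1 − rho)
- ANCOVA on baseline: 1 − rho²

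The ratio of ANCOVA to change score is (1 − rho²) / [2(1 − rho)] = (1 + rho)/2, which is below 1 for every rho below 1. A change score is also worse than the follow-up score alone when rho is below 0.5.

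Unadjusted power of 80% corresponds to a standardised signal of 1.96 + 0.8416 = 2.802. This is a difference of 0.66 SD for 36 v 36 or 0.467 SD for 72 v 72, and the resulting powers are the same for both. Power is Φ(2.802/sqrt(V) − 1.96), with V taken from the list above. For example, ANCOVA at rho = 0.5 gives Φ(2.802/0.866 − 1.96) = Φ(1.275) = 89.9%.

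| rho | Follow-up only | Change score | ANCOVA | Gain over follow-up only | Gain over change score |
|---|---|---|---|---|---|
| 0.3 | 80% | 65.8% | 83.6% | 3.6 | 17.8 |
| 0.5 | 80% | 80.0% | 89.9% | 9.9 | 9.9 |
| 0.6 | 80% | 87.9% | 93.8% | 13.8 | 5.9 |
| 0.7 | 80% | 95.1% | 97.5% | 17.5 | 2.4 |

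**Dependence on the starting power.** At rho = 0.5 the gain over a follow-up-only analysis is 8.1 points from 30% power, 11.9 from 50%, 12.4 from 60%, 11.8 from 70%, 9.9 from 80% and 6.3 from 90%.

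**In terms of precision.** At rho = 0.5 the residual variance falls by 25%. Intervals narrow by 1 − sqrt(0.75) = 13%. The gain matches raising the total from 144 to 144/0.75 = 192. All three figures depend on that rho.

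These are normal-theory results. They do not measure the loss on the Kruskal-Wallis route, where it is enough to note that the test has no place for a covariate.

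**The case against.** The strongest reply is that the Results Analysis section is one general paragraph that mentions neither questionnaire, and that covariates for secondary scores are often left to a statistical analysis plan. That has force against calling the matter an omission. It has less against the tests that are named: Kruskal-Wallis excludes a covariate, and a two-way ANOVA includes none unless one is added.

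Several stronger readings are tempting and should be resisted.

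- **That the plan ignores the baseline altogether.** This is not established. A group-by-time layout is not ruled out, and it would use the baseline, though less efficiently than ANCOVA.
- **That about 10 points of power are lost.** This needs rho near 0.5 and 80% starting power. The Protocol states neither for these scores. Its 80% belongs to complete lesion response, and rho may differ between the two questionnaires and with follow-up time. If the analysis is a change score and rho is 0.7, the loss is only about 2 points.
- **That the results would be biased.** Allocation is randomised, so the unadjusted tests keep their validity and their type I error rate.
- **That the scores will go to Kruskal-Wallis.** Bounded sums may fail a normality check, but the Protocol gives no distribution.

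**Conclusion.** The point holds as a matter of efficiency. Both scores are measured at baseline in everyone, the named methods make no stated use of them as a covariate, and ANCOVA has smaller variance on either reading of the two-way ANOVA, apart from one degree of freedom. A follow-up-only analysis also loses nothing if rho is zero.

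The size is conditional. From an assumed 80% unadjusted power, the gain is about 4 to 18 points over a follow-up-only analysis for rho from 0.3 to 0.7. At rho = 0.5 it is about 6 to 12 points for starting power between 30% and 90%. Against a change score the gain runs the other way, from about 18 points at rho 0.3 to about 2 at rho 0.7.

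The primary conclusion is unaffected. The conflicting follow-up times are a separate defect in the same outcomes, and they must be settled first because the model and rho both depend on the time point.

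**What to change.** In Results Analysis, state that each post-treatment AKQoL and FACE-Q score is compared by ANCOVA. The terms are concentration, incubation time, their interaction and the participant's own pre-treatment score on the same questionnaire. Report adjusted mean differences with 95% confidence intervals. Judge normality on the model residuals. If they are clearly non-normal, use rank-based ANCOVA or bootstrap intervals in place of Kruskal-Wallis, so that the baseline stays in the model.

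Reconcile the assessment times of both questionnaires across the Abstract, section 2.2 and section 3.10, and name the time points to be analysed.

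The cost is a sentence or two of text, one degree of freedom, and a simple rule for a missing baseline score, such as mean imputation of that covariate. No new data, visits or participants are needed.
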